### Work package 3: quantitative outcome assessment

A quantitative outcome assessment will test hypotheses that the presence of PDD schemes in police force areas reduce adverse health and offending outcomes for drug-involved suspects. The analysis will involve comparing outcomes for cohorts of drug-involved suspects eligible for diversion in our three focus areas (i.e. police forces with PDD schemes), with those for cohorts of similar individuals in three comparison areas (i.e. forces without PDD schemes) that are in groups of police forces that are most comparable to the intervention forces (HMICFRS, 2023).

Participants in our quantitative analysis will be individuals who had contact with the police in relation to illicit drugs, who may have been eligible for diversion (regardless of whether diversion was available, offered or taken up by that individual). Each PDD and comparison police force will identify individuals who had contact with the police for a qualifying offence between 1 October and 2021 and 30 September 2022 and were aged at least 18 years. Qualifying offences will be (a) simple possession of any controlled drug (personal use), and (b) any of: shoplifting, assault, criminal damage, criminal damage without intent to commit, possession of drugs, drunk and disorderly, drunk and incapable, any theft (other than burglary); in combination with a suspected or proven offence in contravention of the Misuse of Drugs Act 1971 or the Psychoactive Substances Act 2016, in the preceding 3 years, OR a flag in police records for involvement with illicit drugs.

We will use two primary outcomes for health and reoffending:

Health—the count of hospital episodes (including unplanned/emergency inpatient admissions and emergency department visits) during the follow-up period that are related to drugs, alcohol, or accidents.Reoffending—a count of how many offences participants commit in the follow-up period, as recorded in the PNC and adjusted for the time that each participant was in the follow-up period.

We will also use the following secondary outcomes:

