Health—the measures will be (a) any entry into structured treatment for drug or alcohol use in a community setting during the follow-up period; and (b) retention in treatment for at least 28 days for those who start drug or alcohol treatment.Reoffending—(a) a dichotomous measure of any offending, with analysis offset by the duration of follow-up, and (b) a measure of the total social cost of these crimes, calculated using the costs attributed to each type of crime according to Home Office estimates of the social costs of each type of crime (Heeks et al., 2018).

The data for the quantitative impact assessment will be compiled using individual-level data linkage between databases of administrative records. Participating police forces will share lists of eligible individuals with the Department of Health and Social Care (DHSC), which is a partner in the project. The DHSC will link the data to four national health and criminal justice databases, and then pseudonymise the data before analysis within a secure data system. The four national databases will be:

The Police National Computer, which will be used to derive a measure of historical offending at study entry, and the primary and secondary reoffending outcomes;The National Drug Treatment Monitoring System, which will be used to measure secondary health outcomes (i.e. entry to and retention in drug and alcohol treatment services);Hospital Episode Statistics, which will be used to measure our primary health outcome (i.e. hospital episodes) (Herbert et al., 2017).The Office for National Statistics mortality database, which we will use to identify participants who die during the follow-up period and are to be excluded from our analysis. Deaths will only be used to censor follow-up and not as an outcome because their relative rarity would result in a lack of statistical power for detecting significant effects.

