We plan to use multivariable regression to estimate the effect of PDD on primary and secondary outcomes. Our analysis will control for potential confounders including age, sex/gender, ethnicity, health, previous experience of drug or alcohol treatment, offending history, reason for police contact, date of cohort entry, and the force-level baseline probability of each outcome. Our primary outcomes are count variables, and we will therefore use a mixed negative binomial model offset by the logged duration between the study entry date and the end of follow-up. We plan to use a negative binomial model rather than a Poisson model because we anticipate that both outcomes will be overdispersed, with some participants having high counts.

In our primary analysis, we will compare outcomes for all drug-involved suspects eligible for diversion in our focus areas (regardless of whether they were offered or took up diversion) with those for similar suspects in control areas. This is akin to an ‘intention to treat’ design in an experimental study (Hernán & Robins, 2016).

In our secondary analyses, we will:

Compare outcomes for participants who are diverted with those who are not. This is comparable to a ‘per protocol’ analysis in experimental trials (Hernán & Robins, 2016);Report access to diversion by age, sex, ethnicity, and socioeconomic status (as a complement to work package 5 on equity of effects).Test whether the effectiveness of diversion for each outcome varies by police force (while acknowledging that this analysis will have lower statistical power).

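### Two incompatible rules for participants who die: adjacent sentences exclude them and censor them; the plan should say censor

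*Protocol article*

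**What the plan says.** All the relevant text is in the protocol article, Work package 3: quantitative outcome assessment.

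- **Exclusion.** The Office for National Statistics mortality database is to be used to "identify participants who die during the follow-up period and are to be excluded from our analysis".
- **Censoring.** The sentence that follows reads "Deaths will only be used to censor follow-up and not as an outcome". The reason given for not making death an outcome is that "their relative rarity would result in a lack of statistical power for detecting significant effects".
- **Health outcome.** The primary measure is "the count of hospital episodes (including unplanned/emergency inpatient admissions and emergency department visits) during the follow-up period", limited to episodes related to drugs, alcohol or accidents.
- **Reoffending outcome.** The primary measure is a count of recorded offences, "adjusted for the time that each participant was in the follow-up period".
- **Model.** Both primary outcomes go into a "mixed negative binomial model offset by the logged duration between the study entry date and the end of follow-up".
- **Population.** The primary analysis will "compare outcomes for all drug-involved suspects eligible for diversion in our focus areas (regardless of whether they were offered or took up diversion", and the article likens this to intention to treat.

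**The concern.** A person who has been excluded has no follow-up left to censor, so the two sentences give different analysis sets for both primary outcomes. The article does not leave this rule to a later document. It states it twice, differently.

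If the exclusion sentence were followed:

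- Membership of the analysis set would depend on an event after cohort entry, which conflicts with comparing all eligible suspects.
- Exposure might influence who is dropped. The Background says diversion can lead people to treatment services that are effective in preventing death.
- Every hospital episode and offence before death would be lost. The Background names overdose as a harm in this population, and drug-related episodes are part of the primary health outcome.
- Work package 4 builds its costs on these outcomes, so hospital costs before death might be lost as well.

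**Working it through.** The article states no death rate, event rate or sample size, so there is no figure of its own to reproduce. The first step is a reading of the text; the second is an illustration on assumed inputs.

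**1. Which rule fits the rest of the plan?**

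| Element of the plan | Exclusion | Censoring |
|---|---|---|
| Offence count adjusted for each person's own time in follow-up | Not needed for deaths | Fits |
| Log-duration offset | Not needed for deaths | Fits |
| Comparison of all eligible suspects | Conflicts | Fits |
| Deaths used only to censor | Conflicts | Fits |

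**2. How far apart could the two rules be?** All inputs here are assumptions. A fraction m of each group is frail, with event rate k; everyone else has rate 1. In the comparison areas all frail people die halfway through follow-up. Under diversion 75% of them do, and the other 25% survive at rate k. Diversion has no other effect. The length of follow-up cancels.

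Exclusion:
- comparison rate = 1
- diversion rate = [(1−m) + 0.25mk] / [(1−m) + 0.25m]

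Censoring at death:
- comparison rate = [(1−m) + 0.5mk] / [(1−m) + 0.5m]
- diversion rate = [(1−m) + 0.625mk] / [(1−m) + 0.625m], where 0.625 = 0.75×0.5 + 0.25

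For m = 2%, k = 8:
- Exclusion: (0.98 + 0.04)/(0.98 + 0.005) = 1.0355
- Censoring: (1.08/0.9925)/(1.06/0.99) = 1.0882/1.0707 = 1.0163
- Exclusion relative to censoring: 1.0355/1.0163 = 1.019

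| m | k | Rate ratio, exclusion | Rate ratio, censoring | Exclusion ÷ censoring |
|---|---|---|---|---|
| 1% | 4 | 1.0076 | 1.0037 | 1.004 |
| 1% | 8 | 1.0176 | 1.0084 | 1.009 |
| 2% | 4 | 1.0152 | 1.0073 | 1.008 |
| 2% | 8 | 1.0355 | 1.0163 | 1.019 |

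Exclusion lowers the comparison-group event rate by 1.5% (m = 1%, k = 4: 1 − 1/1.0151) to 6.6% (m = 2%, k = 8: 1 − 1/1.0707).

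**3. Sensitivity to the assumptions.**

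- With a 10% instead of a 25% cut in deaths, exclusion ÷ censoring is 1.0015 to 1.0077.
- With 1-2% deaths and the 25% cut, but only 10% of frail people dying in the comparison areas, it is 1.003 to 1.007.
- Now suppose those spared from death have the ordinary survivor rate and diversion halves mortality from 1%. Exclusion gives 1.000. Censoring gives 0.995 (k = 3), 0.990 (k = 5) and 0.978 (k = 10). At 3% mortality and k = 10 censoring gives 0.939.
- In a simulation with death hazard proportional to a gamma-distributed episode rate, a true ratio of 0.80 and about 1% deaths, exclusion gave 0.802 and censoring 0.800.
- In the arithmetic of the third item, with equal mortality in both groups or with k = 1, the two rules give the same rate ratio.

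**The case against.** The strongest reply is that the text already leans to censoring. The second sentence is restrictive: deaths are used only to censor. The time adjustment is personal, and the comparison takes in everyone eligible. On that view, excluded is loose wording for censored and the harm never occurs. This largely stands as a guess at intent. It does not remove the first sentence, which an analyst could follow as written.

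Three stronger readings are tempting, and the documents do not support them.

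- **That the sickest people's episodes will be removed.** A reader might infer this from the exclusion sentence alone. It happens only if that sentence governs, and no figure in the article shows that those who die have higher event rates.
- **That people who die would be credited with time after death,** because the offset is "offset by the logged duration between the study entry date and the end of follow-up". If death censors follow-up, a person's follow-up ends at death, and the time adjustment is already specific to each participant. The end date should be made explicit, but no separate error is shown.
- **That exclusion could hide a third of a true 10% reduction.** This takes the whole 1.0355 from the most extreme case. Censoring itself gives 1.0163 there, so exclusion adds about 1.9%, roughly a fifth.

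It is also fair to say that the assumed mortality effect has no support in the article. Exposure is the presence of a scheme in the area, whatever the offer or uptake, and the Background credits prevention of death to treatment services, not to that contrast.

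**Conclusion.** The contradiction is real, is in the current text, and concerns both primary outcomes. Censoring is the rule consistent with the rest of the plan. Exclusion would condition on a post-exposure event and discard events before death.

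The numerical stake is probably small: about 0.4-1.9% on the rate ratio under the assumptions of step 2, and less under several milder ones. It arises only if mortality differs between diversion and comparison areas and people who die have different event rates from survivors. The article gives neither quantity and calls deaths relatively rare, so the size cannot be established from it.

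In both arithmetic models, if diversion prevents deaths among people with higher rates, exclusion moves the ratio against diversion relative to censoring. Which of the two estimates counts as biased depends on the target quantity. In the model where those spared have ordinary rates, exclusion returns 1.000 and it is censoring that moves. A general claim that exclusion biases the result against diversion is therefore not supported.

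**What to change.** In Work package 3:

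1. Delete the clause that excludes people who die from the sentence on the mortality database.
2. State that all eligible people are kept, and that hospital episodes and offences are counted up to the earlier of death and end of follow-up.
3. State that the offset ends on that same date: log(min(date of death, end of follow-up) − entry date).
4. Give a separate rule for death before day 28 in the treatment-retention outcome. A count with a log-time offset does not suit that measure.

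The cost is wording only, because mortality linkage is already planned. The change is best made before outcome data are seen.

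### The primary PDD effect rests on three forces against three, so usual Wald z inference from the mixed negative binomial model would be anti-conservative; a t reference on 4 or 3 between-force degrees of freedom is needed.

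*Protocol article*

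**What the plan says.** All of this is in the protocol article, Work package 3.

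- **Hypothesis.** The test is whether "the presence of PDD schemes in police force areas reduce adverse health and offending outcomes" for drug-involved suspects.
- **Comparison.** Cohorts from three forces with schemes are compared "with those for cohorts of similar individuals in three comparison areas", the latter being forces without schemes. Each force supplies one 12-month entry cohort; no individual-level cohort from before the schemes is described.
- **Primary contrast.** All eligible suspects in the focus areas are included "regardless of whether they were offered or took up diversion".
- **Model.** For the two primary outcomes, "we will therefore use a mixed negative binomial model", with log follow-up time as offset. The article does not give the level of the random effect, the estimator or the reference distribution.
- **Covariates.** These are individual characteristics "and the force-level baseline probability of each outcome".
- **By-force analysis.** One secondary analysis is to "Test whether the effectiveness of diversion for each outcome varies by police force". Reduced power is acknowledged here, and only here.

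**The concern.** The exposure in the primary contrast does not vary within a force. Everyone in a scheme force is exposed and everyone in a comparison force is unexposed, in a single cohort. The sampling unit for the effect is therefore the force, and there are six.

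A random intercept for force puts between-force variation into the standard error, but that variance is then estimated from 4 or 3 residual degrees of freedom. Wald z inference treats it as known, and ML also underestimates it. Both errors make the interval too narrow. Linking more people shrinks only the within-force part and cures neither.

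The Dissemination section makes national policing guidelines conditional on a positive impact and says the reports may support Treasury business cases. An inflated false-positive rate bears directly on those decisions. A reader of the article would also gather that few forces limit only the secondary by-force analysis.

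**Working it through.** The article states no sample size, alpha or between-force variance, so there is no figure of its own to reproduce.

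**Inputs from the article:** 3 exposed forces, 3 unexposed forces, one force-level covariate.

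**Assumed:** two-sided nominal 5%; between-force SD of the log rate (τ) 0.05 to 0.30; for the simulation, 1,000 suspects per force, mean count 0.6 and negative binomial dispersion 2 (variance = mean + 2 × mean²).

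**1. Degrees of freedom.** Six forces less intercept and PDD: 6 − 2 = 4. With the force-level baseline: 6 − 3 = 3. The two-sided 5% critical values are 2.78 and 3.18, against 1.96. For the same standard error the interval on the log scale is 2.776/1.96 = 1.42 times as wide (4 df) or 3.182/1.96 = 1.62 times as wide (3 df).

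**2. Limiting type I error of the Wald z test when between-force variation dominates.** With a REML-type variance the statistic follows t on df, so the error is P(|t_df| > 1.96). ML divides the residual sum of squares by 6 instead of df, so the error is P(|t_df| > 1.96 × √(df/6)).

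| | REML, z | ML, z |
|---|---|---|
| No force covariate (4 df) | P(\|t\| > 1.96) = 0.122 | P(\|t\| > 1.600) = 0.185 |
| With force covariate (3 df) | P(\|t\| > 1.96) = 0.145 | P(\|t\| > 1.386) = 0.260 |

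**3. Simulation under a null PDD effect.** A negative binomial model with a force random intercept was fitted by ML, with 400 runs per cell (Monte Carlo SE about 0.02). A t test on the six force log rates was run on the same data.

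| τ | ML z, no covariate | ML z, with covariate | Force-level t, without / with |
|---|---|---|---|
| 0.05 | 0.108 | 0.133 | 0.055 / 0.055 |
| 0.10 | 0.155 | 0.198 | 0.045 / 0.055 |
| 0.20 | 0.165 | 0.265 | 0.048 / 0.040 |
| 0.30 | 0.188 | 0.260 | 0.068 / 0.070 |

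The z test approaches the limits in step 2. The t test stays near 5%.

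**4. If no force effect were fitted.** The within-force variance of a log rate is (0.6 + 2 × 0.36)/0.36/1,000 = 0.00367. The design effect is 1 + τ²/0.00367: 1.68 at τ = 0.05, 3.73 at 0.10, 11.9 at 0.20 and 25.5 at 0.30. The error, 2 × P(Z > 1.96/√design effect), is 0.13, 0.31, 0.57 and 0.70.

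**5. Precision with unlimited suspects.** The standard error tends to τ√(1/3 + 1/3) = τ√(2/3). At τ = 0.10 this is 0.0816. The 95% limits are then a factor exp(2.776 × 0.0816) = 1.25 either side (4 df) or exp(3.182 × 0.0816) = 1.30 (3 df), against exp(1.96 × 0.0816) = 1.17 with z. If the covariate differs between arms or explains between-force variation, the 3 df figure changes.

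**The case against.** **The article does not say Wald z will be used.** This is the strongest objection. The article is condensed, and the estimator and any small-cluster method may stand in a fuller plan that is not shown. A reader might infer that the published p-values will be too optimistic; the text does not support that, and the inflation is conditional on default inference. Nor does it show that a force effect will be left out: the word mixed suggests that clustering is meant to be modelled, so step 4 is a warning and not a description of the plan. What remains is a design fixed in the article itself: exposure constant within force, six forces, and a force-level covariate that uses a fourth of the available degrees of freedom.

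**The size depends on a between-force variance that nobody has stated.** This also stands. Comparison forces come from the most similar groups, and adjustment could shrink what is left. At τ = 0.05 the error is roughly twice nominal, not five times.

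**The by-force analysis.** A reader might infer that it cannot be identified at all. That is true only if it concerns scheme presence, since a force-specific effect then cannot be separated from that force's own level. The wording is about the effectiveness of diversion, and the analysis is listed after the diverted-versus-not comparison. Read that way, variation by force can be estimated within the scheme forces, though it is open to selection.

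**The force-level baseline.** A reader might infer that it will adjust the effect away. The article gives neither the baseline period nor the schemes' start dates. The Background mentions earlier trials of schemes in Durham and the West Midlands, so a baseline that post-dates a scheme is possible, but it is not stated.

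**Permutation.** A three-against-three permutation test cannot go below a two-sided p of 2/20 = 0.10. No such test is planned, so this illustrates how little six forces can show and is not an error in the plan.

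**Conclusion.** The point holds in conditional form. The primary effect has 4 between-force degrees of freedom, or 3 with the planned force-level covariate. Under usual Wald z inference, the type I error at nominal 5% tends to about 12% (REML) or 18% (ML) without the covariate and 14% or 26% with it. At an assumed SD of 0.05 and 1,000 suspects per force, simulated ML error is about 11-13%. It would be higher still if no force effect were fitted and between-force variation were more than slight.

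The degrees of freedom follow from the article. The limiting rates need only the choice of z inference and dominant between-force variation. Everything between rests on the assumed SD, cohort size, mean and dispersion. The article should also acknowledge that six forces limit the primary inference, not just the by-force analysis.

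**What to change.** 1. Specify a random intercept for police force in the primary models.
2. Test the PDD effect and form its interval with a t reference on between-force degrees of freedom (4, or 3 with the baseline covariate), using a REML-type variance or an equivalent two-stage force-level analysis.
3. State that the primary inference is limited by six forces.

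Two conditional additions:

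- State which contrast the by-force analysis uses. If it is scheme presence, report it descriptively without p-values.
- Take the force-level baseline from before each scheme began, where such data are available, because a later baseline could absorb part of the effect. Work package 2 already requests aggregate police data from three years before each scheme, though not these outcomes.

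**Cost.** Items 1 to 3 change analysis wording only; a pre-scheme baseline may need further data. The real price is power. The rate ratio detectable at 80% power with unlimited suspects is exp(−δ × τ√(2/3)), with noncentrality δ = 3.76 (4 df) or 4.26 (3 df). That gives about 0.86 or 0.84 at τ = 0.05, 0.74 or 0.71 at 0.10, and 0.54 or 0.50 at 0.20. The loss reflects what six forces can support.

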### Work package 5: equity assessment

In the light of concerns over health inequalities and ethnically disproportionate policing (Shiner et al., 2018), we will carry out an assessment of the equity aspects of our focus PDD schemes. This work package will draw on data collected for work packages two and three, and so will have the same participants. Quantitatively, we will test the hypotheses that there are significant differences in the proportion of eligible suspects that are offered diversion away from criminalisation by gender and ethnicity. We will also test the hypotheses that there are similar differences among suspects who are offered diversion in terms of: attending diversion; completing it successfully; and ending up with OOCDs or criminal sanctions for suspected offences. This will enable us to assess whether PDD leads to ‘net-widening’ and ‘mesh-thinning’ in these areas. These two phenomena, originally identified by Cohen (1979), refer to processes whereby purported alternatives to criminalisation can actually bring more people into the net of penal control and increase the obligations placed upon them. Given the known disproportionality of drug law enforcement in England and Wales (Shiner et al., 2018; Stevens, 2011), it is possible that these processes have more of an impact on people who are racialised as Black. We will seek to examine this possibility in both the aggregate data, and in the individual-level data collected for Work Package 3, although we are not yet certain that the individual-level data will include information on ethnicity to do so.

Using the qualitative data collected for the second work package, we will also look for any differences in the processes and reported outcomes of PDD schemes for people with other protected and PROGRESS + characteristics (O’Neill et al., 2014). These include place of residence, race/ethnicity, occupation/class, gender/sex, religion, education, socio-economic status, social capital, age, disability, time-dependent characteristics (e.g. educational transitions, leaving home), and relevant personal circumstances (e.g. previous experiences of local authority care and contact with the criminal justice system).

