### Work package 6: realist synthesis

In this final work package, we will bring together all our findings in the form of a realist synthesis of what works, for whom, in what circumstances and why. To do this we will employ the EMMIE and VICTORE framework (Cooper et al., 2020; Johnson et al., 2015). Taken together, the work packages provide detail on all the components of these framework.

Effect is synonymous with outcomes and so data from work packages 3 (quantitative outcome assessment) and 5 (equity assessment) will be used here. The Mechanisms, Moderators and Implementation are central to the delivery of the process evaluation in work package 2. Work package 4 will detail the economics of PDD in the form of the CCA. Our analysis in work package 2 also employs the VICTORE framework to sensitise us to issues of Volition (the intentions and choices of people involved in the PDD schemes), Time (including changes in implementation over time), Rivalry (the presence and effects of similar or competing interventions for the target group), and Emergence (the features of PDD schemes that arise from the combinations of other factors). Work packages 2 and 5 will provide detail on the implementation of PDD schemes. Work package 4 will detail the economics of PDD in the form of the CCA.

As realism encourages us to think beyond ‘what works’, in our synthesis we will unpack what it is about PDD that leads to the observed pattern of outcomes. In other words, we do not view exposure to PDD as an independent variable that can be experimentally closed off from all other factors (Deaton & Cartwright, 2018). We are interested in what it is about PDD schemes that produce outcomes in particular contexts. In this sense, the findings of the realist synthesis will enable us to refine further the programme theory in Fig. 1 and then use this as the platform for developing actionable guidance for the future rollout of PDD programmes.

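### The secondary diverted-versus-not-diverted comparison is an as-treated contrast, not a per-protocol one, and should not be read as the effect of diversion

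*Protocol article*

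**What the plan says.** All of this is in the protocol article. Under *Work package 3: quantitative outcome assessment*, the primary analysis is an area-level contrast. It compares all eligible suspects in the focus forces, "regardless of whether they were offered or took up diversion) with those for similar suspects in control areas". The first secondary analysis is to "Compare outcomes for participants who are diverted with those who are not", and the text adds: "This is comparable to a ‘per protocol’ analysis in experimental trials".

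The regression controls for age, sex/gender, ethnicity, health and previous drug or alcohol treatment, and for "offending history, reason for police contact, date of cohort entry, and the force-level baseline probability of each outcome". For the count outcomes the model is a "mixed negative binomial model offset by the logged duration between the study entry date and the end of follow-up". Cohort members are people who "had contact with the police for a qualifying offence between 1 October and 2021 and 30 September 2022".

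Other sections show that being diverted is not automatic:

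- *Work package 1* used vignettes in which officers explained when they would and would not apply a diversion.
- *Work package 2* plans interviews with eligible people who were not diverted or are not taking part.
- *Work package 5* will test whether "there are significant differences in the proportion of eligible suspects that are offered diversion away from criminalisation by gender and ethnicity".
- *The evaluated PDD schemes* restricts eligibility in the West Midlands and Thames Valley to simple possession. The work package 3 cohort also admits shoplifting, assault, theft and other offences when combined with recent drug offending or a drug flag.

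**The concern.** A per-protocol analysis keeps the strategies being compared (here, a force with a scheme against a force without one) and deals with non-adherence inside each. The planned contrast drops that structure and sorts people by treatment received. Three things can then separate the two groups even if diversion does nothing:

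1. **Selection.** Officers decide whether to apply diversion and suspects decide whether to engage. As the cohort is written, some members in two of the three focus forces fall outside their scheme's eligibility and can only be in the not-diverted group.
2. **Incomplete adjustment.** The covariate list has no variable for offer or willingness. Ethnicity is listed, but *Work package 5* is not certain that the individual-level data will contain it.
3. **Timing.** The offset runs from study entry, whereas diversion follows police contact. If what happens in between affects who is diverted, the groups are partly defined by the outcome.

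The article attaches a power caveat to the by-force analysis in the same list, but no selection caveat here. *Dissemination* says the findings may support spending cases and that national guidelines depend on a positive impact. A result labelled per-protocol invites reading as the effect of actually being diverted.

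**Working it through.** The article gives no sample size, power, uptake, event rate or risk gradient for this analysis, so there is no plan figure to reproduce. Each step below assumes **no true effect** and asks what the contrast would show. All rates and uptakes are assumptions.

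**Step 1: selection, unadjusted.** Let people who would be diverted have event rate 1 and the others rate *r*, with uptake 0.4 and focus and comparison cohorts of equal size. If the not-diverted group includes the comparison forces, its mean rate is (0.6*r* + 0.4 + 0.6*r*)/1.6.

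| *r* | Mean rate, not diverted | Rate ratio, pooled | Focus forces only (1/*r*) |
|---|---|---|---|
| 1.25 | 1.9/1.6 = 1.1875 | 0.84 | 0.80 |
| 1.5 | 2.2/1.6 = 1.375 | 0.73 | 0.67 |
| 2 | 2.8/1.6 = 1.75 | 0.57 | 0.50 |
| 0.8 (higher-need people diverted) | 1.36/1.6 = 0.85 | 1.18 | 1.25 |

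Confining the contrast to focus forces makes the comparator clearer but the bias larger. Weaker selection does little harm. With half the suspects low-risk, uptake of 50% in low-risk and 40% in high-risk suspects, and a 1.5-fold rate difference between them, the focus-force rate ratio is 0.96.

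**Step 2: selection, adjusted.** A simulation used 40,000 people, half in focus forces, with 50% uptake. A measured covariate and an unmeasured trait could drive both uptake and outcome. The model was a negative binomial regression (dispersion 1, no random effects) adjusted for the measured covariate only. Ranges are across the settings run, for the contrast within focus forces.

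| Unmeasured trait (log-rate per SD; uptake log-odds per SD) | Adjusted rate ratio |
|---|---|
| No effect on outcome (0; 0.8) | 0.98–1.03 (crude 0.64–0.83) |
| Moderate (0.4; 0.8) | 0.77–0.85 |
| Strong (0.6; 1.0) | 0.62–0.82 |

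The area-level contrast stayed at 0.98–1.04 throughout, because the simulated areas were balanced at baseline. So adjustment can remove the bias entirely, but only if the covariates capture the selection.

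**Step 3: timing alone.** Suppose uptake is unrelated to risk, but a person who reoffends before diversion is delivered is no longer diverted. Let individual rates follow a gamma distribution with shape 1 and mean *m* per year, follow-up be one year, the lag be *L* years and uptake be *u*. Then:

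- Probability of no event before delivery: p = 1/(1 + *mL*).
- Mean events per diverted person: d = *m*p(1 − *L*).
- Proportion diverted: q = *u*p.
- Mean events per person not diverted in focus forces: n = (*m* − q d)/(1 − q).

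Example with *m* = 0.5, *L* = 1/12, *u* = 0.4: p = 0.96, d = 0.44, q = 0.384, n = (0.5 − 0.169)/0.616 = 0.537, and d/n = 0.82.

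| Lag | *u* = 0.4; *m* = 0.5, 1 | *u* = 0.6; *m* = 0.5, 1 |
|---|---|---|
| 1 month | 0.82, 0.78 | 0.76, 0.71 |
| 3 months | 0.56, 0.50 | 0.48, 0.44 |

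Baseline covariates do not correct this, because it comes from the time origin and not from differences at entry.

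**The case against.** Much can be said for the plan. The article says only *comparable to* per-protocol, and the analysis is secondary. An article commonly leaves the exact definitions of diverted and of the comparator to a fuller plan. The covariates, especially offending history and reason for contact, plausibly predict both outcome and diversion, and step 2 shows the bias disappearing when they capture the selection. Gender and ethnicity, the two factors tested in *Work package 5*, are both on the adjustment list.

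These points limit the size of the problem but do not change the label. The contrast is still by treatment received, and no caveat about selection is given.

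The text does not support four stronger readings:

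- **That the contrast is bound to flatter the scheme.** The article gives no risk gradient, and *r* below 1 reverses the bias.
- **That comparison-force suspects are certainly pooled with the not-diverted.** The sentence taken literally allows it but does not say so.
- **That early reoffending removes the chance of diversion.** No section states this. Diversion is described as an alternative to prosecution for the suspected offence, so the lag may be short. Step 3 shows what would follow if such a rule operated.
- **That the contrast must be replaced by an instrumental-variable estimate.** That is a trade-off. With three forces against three, dividing by 40% uptake multiplies any residual area-level bias in the rate difference by 1/0.4 = 2.5.

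**Conclusion.** The concern holds as a matter of labelling and interpretation. The secondary contrast is as-treated, and the article itself shows that offer and uptake depend on decisions by officers and suspects. With no true effect it can show an apparent benefit or an apparent harm.

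The size cannot be fixed from the article. Steps 1 to 3 range from essentially no bias, when the covariates capture the selection and timing is handled, to rate ratios near 0.5 under strong selection or a three-month blocking lag. The 0.84–0.57 illustration rests on 40% uptake, equal cohorts, the pooled comparator and no adjustment, whereas the planned analysis is adjusted. It shows what is possible and does not predict the result.

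The area-level primary analysis does not depend on individual uptake, so this problem does not touch it.

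**What to change.** Change the work package 3 text, and any fuller analysis plan, as follows:

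1. Call the contrast as-treated and exploratory, and drop the per-protocol comparison.
2. State what counts as diverted (offered, accepted, attended or completed) and who is in the comparator, including whether comparison forces are in it. Say how cohort members outside a scheme's eligibility are handled.
3. Count diversion as exposure only from its date, as a time-varying exposure or with a landmark.
4. State that the result is not to be read as the causal effect of diversion, and that conclusions rest on the area-level analysis.
5. Optionally, add as a sensitivity analysis the area-level rate difference divided by the proportion diverted in focus forces. State that it assumes schemes act only through diversion, is imprecise with six forces, and magnifies any residual area-level confounding.

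Cost: mostly wording. The forces must supply a diversion date if they do not already, and the secondary result carries a weaker interpretation.
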